### Intervention

2.4

All patients will be managed similarly in the preoperative period. Supplementation with vitamin D will be recommended for patients with 25-OH vitamin D deficit (< 20 ng/mL). None of the patients will receive preoperative calcium supplementation. The protocol for standard thyroidectomy includes starting with luxation of each thyroid lobe and performing careful dissection to minimize damage to the parathyroid glands, followed by search and visual identification of the glands in each lobe, as well as in orthotopic localizations.

#### ICG angiography-guided thyroidectomy

2.4.1

All the participant surgeons will conduct a formative meeting with the leading group to homogenize the procedures and the definitions. The procedure will include performing an ICG angiography of the parathyroid glands before removal of the thyroid gland. To this purpose, after the luxation of the thyroid lobe and the identification of the parathyroid glands, 1 mL of the contrast material will be administered through a peripheral vein after dilution of a powdered vial of 25 mg (Verdye^®^, Diagnostic Green GmbH, Aschheim-Dornach, Germany) of ICG in 10 mL of sterile water. After a few seconds, ICG-enhanced fluorescence imaging of the vascular pattern of the parathyroid glands previously identified will be acquired using a near-infrared camera. Visualization of the vascular pattern of the parathyroids will include identification of a clear feeding vessel with its pedicle (defined pattern) or a vascular network around the parathyroid gland without a clear feeding vessel (non-defined pattern). After identification of the vascular map of each parathyroid gland, the dissection will be performed in a guided manner to minimize its damage. The surgical procedure will continue with total removal of the thyroid lobe and then performing an ICG angiography of the parathyroids after injection of 3 mL of the contrast material, and obtaining a black and white near-infrared view. The fluorescence of the glands (back and white imaging) will be assessed intraoperatively by the operating surgeon, and the degree of fluorescence will be classified according to the color of the gland reflecting the degree of perfusion. The color of the gland can vary from black (suggesting that it is not vascularized and likely non-viable), to white (suggesting that it is well vascularized and viable). Glands will be classified as 0, black (nonvascularized); 1, gray/heterogeneous (partially vascularized); and 2, white (well vascularized). Both autotransplanted and parathyroid glands identified in the histopathological report are devascularized and will be scored as 0. The procedure will be the same in the other lobe, but the initial doses will be 3 mL. During the dissection, repeated doses to reevaluate the vascularization are allowed when needed until a maximum of 5 mg/kg. In patients undergoing central neck dissection, ICG angiography to assess the degree of parathyroid glands vascularization will be performed after each procedure, lymphadenectomy and thyroidectomy.

#### Conventional thyroidectomy

2.4.2

Conventional thyroidectomy will include identification of the parathyroid glands visually (naked eye) and performing a total thyroidectomy followed by an ICG angiography of the parathyroids (as described in the angiography-guided thyroidectomy), assessing the fluorescence the glands and scoring the color reflecting the degree of vascularization as 0, 1, or 2. In patients undergoing central neck dissection, ICG angiography will be performed also after each procedure, lymphadenectomy and thyroidectomy.

In both ICG angiography-guided and conventional thyroidectomy, the case report form will be completed at real time at the end of surgery.

### Postoperative care and follow-up

2.5

During hospitalization, the clinical course of patients will be controlled to assess the presence of hypoparathyroidism, complications, or adverse events (16). Intact parathyroid hormone (iPTH) levels will be measured at 24 hours postoperatively (i.e. the morning after surgery) according to the technique used at each hospital laboratory. Corrected serum calcium levels will be measured 24 hours after surgery. Clinical practice guidelines of each center will be followed for postoperative administration of calcium and vitamin D. Those patients with postoperative hypoparathyroidism will be followed clinically in association with periodical measurements of iPTH, corrected serum calcium, and vitamin D levels at 1, 3, 6, and 12 months after surgery or until hypoparathyroidism resolution.

### Definitions

2.6

Postoperative hypoparathyroidism will be defined by the appearance of symptoms of hypocalcemia after surgery, presence of hypocalcemia (corrected serum calcium levels < 8 mg/dL) in the absence of symptoms, and/or requirement of calcium and/or vitamin D supplementation before this measurement. Permanent hypoparathyroidism will be defined as the need of treatment with calcium and/or vitamin D to maintain corrected serum calcium levels in the normal range or to prevent symptoms of hypocalcemia 12 months after surgery.

An adverse event (AE) will be defined as a medical occurrence in a patient participating in the study, regardless of the causal relationship to the treatment assigned.

### Outcome assessment

2.7

#### Primary outcome

2.7.1

To analyze if those patients included in the experimental group have a lower rate of permanent hypoparathyroidism compared with the control group.

#### Secondary outcomes

2.7.2

(1) To compare the rate of postoperative hypoparathyroidism between both study groups.(2) To compare the number of well-vascularized parathyroid glands (ICG score of 2) remaining *in situ* after thyroidectomy between both groups.(3) To compare the serum levels of iPTH and corrected calcium 24 hours after surgery between both groups.(4) To compare the duration of surgery as the time interval between the start of skin incision and its final closure between both groups.(5) To analyze the influence of the type of vascular pattern (defined or undefined) of the parathyroid glands in angiography-guided thyroidectomy group in the outcomes.(6) To describe the safety profile and adverse events of the ICG angiography.

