### Research setting

2.2

This study will recruit 394 eligible subjects from the Units of Endocrine Surgery of tertiary care hospitals in Spain. The University Hospital of Bellvitge in Barcelona (Spain) will be the reference center. Inclusion and exclusion criteria are shown in **Table 1**.

**Table 1 T1:** Inclusion and exclusion criteria.

**1.- Inclusion Criteria** (1) Patients ≥ 18 years of age with a surgical indication for elective total thyroidectomy with or without central cervical lymph node dissection due to thyroid pathology. (2) The patient has the capacity to understand the study and agrees to participate in it, signing the corresponding informed consent document.
**2.- Exclusion Criteria** (1) Previous surgical intervention on the thyroid or parathyroid gland. (2) Associated hyperparathyroidism that requires associating a parathyroidectomy in the same surgical act. (3) Patients with contraindications for the administration of ICG except for patients with clinical hyperthyroidism, autonomous thyroid adenomas, and focal and diffuse changes of the thyroid gland who will undergo total thyroidectomy. (4) Current drug use or alcohol abuse that could interfere with compliance with the study requirements. (5) Participation in any other drug trials in the month prior to randomization.

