### Randomization and blinding

2.3

After baseline assessment, the study will use a 1:1 ratio to randomly divide the subjects into 2 groups. Randomization will be performed using a computer-generated table of random numbers. The group assignment will be performed by an independent statistician who would be blinded to the recruitment, intervention, and evaluation of participants. Blinding of researchers (who perform the surgical procedures) to group assignment would not be possible to the specific nature of the study. The principal investigator at each participating center will be aware of the randomization arm before entering the operating room. However, statisticians who will perform the statistical analysis after the follow-up of patients will be blinded to group assignment. At the same time, the study is single-blind randomized trial. In this study, all participants will be unaware of the allocation to the experimental or the control group.

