Study variables will be collected by the researchers through clinical visits and results of laboratory analyses. Data will be stored in a codified electronic database specifically designed for the purpose of the study. Monitorization of study data will be performed by external personnel unaware of details of the study. To examine the benefits of identifying the vascular pattern of the parathyroid glands using an ICG angiography before thyroidectomy for preventing permanent hypoparathyroidism, a full analysis set will be performed, that is, all patients randomized who will be operated on, and followed postoperatively until permanent hypoparathyroidism will be resolved or for a maximum of 12 months after surgery. Categorical variables will be expressed as frequencies and percentages, and continuous variables as mean ± standard deviation or median and interquartile range (IQR) (25th-75th percentile). The Shapiro-Wilks test will be used to assess the normal distribution of data and the Levene’s test to assess homoscedasticity. Categorical variables will be analyzed with the chi-square test or the Fisher’s exact test, and quantitative variables with the Student’s *t* test or the Mann-Whitney *U* test according to conditions of application. The risk ratio (RR) and the 95% confidence interval (95%) will be calculated to assess the probability of permanent hypoparathyroidism. Univariate and multivariate logistic regression models adjusted by confounding variables will be performed to identify risk factors for permanent hypoparathyroidism. *P* < 0.05 is set as the significance level. The Statistical Package for the Social Sciences (SPSS) version 26 for Windows will be used for data analysis.

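### Secondary outcome 3 compares 24-hour iPTH and calcium without adjusting for each patient's preoperative value, which costs precision but does not bias the comparison

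*Protocol article*

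**What the plan says.** All references are to the protocol article.

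- **Outcome (2.7.2, item 3):** "To compare the serum levels of iPTH and corrected calcium 24 hours after surgery between both groups". This is an absolute postoperative level, not a change or a percentage fall.
- **Sampling (2.5):** for iPTH, "levels will be measured at 24 hours postoperatively (i.e. the morning after surgery) according to the technique used at each hospital laboratory". For calcium, "Corrected serum calcium levels will be measured 24 hours after surgery". Later samples are for patients with postoperative hypoparathyroidism only: "periodical measurements of iPTH, corrected serum calcium, and vitamin D levels at 1, 3, 6, and 12 months after surgery", or until the condition resolves.
- **Analysis (2.8):** "quantitative variables with the Student’s *t* test or the Mann-Whitney *U* test", chosen according to whether the conditions for each test are met. The only adjusted model in that section is a logistic regression for permanent hypoparathyroidism, which is a different outcome.
- **Before surgery (2.3, 2.4):** "After baseline assessment, the study will use a 1:1 ratio to randomly divide the subjects into 2 groups". The content of that assessment is not listed. The only preoperative laboratory value named anywhere is 25-OH vitamin D, in 2.4.

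**The concern.** A 24-hour iPTH or calcium value reflects both where the patient started and what the operation changed. A two-sample test on that value counts all the variation in starting level as noise. If patients who start high also tend to end high, part of that noise is predictable and could be removed by adjusting for the preoperative value. The stated method does not do so.

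For iPTH there is a second source of noise. Each hospital uses its own technique, so assay differences between hospitals enter the pooled comparison. A preoperative value from the same laboratory carries the same assay differences, and adjusting for it would absorb part of them.

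At stake is the width of the confidence interval for this outcome, and the loss of a simple way to correct for a chance difference in starting level between the arms.

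**Working it through.** **The plan's own figure.** No effect size, standard deviation or power is stated for secondary outcome 3. The only sample size is that for the primary outcome in 2.8: 8% versus 2%, alpha 5%, power 80%, about 5% loss, 197 per arm. A two-sided arcsine calculation reproduces it:

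- h = 2·arcsin(√0.08) − 2·arcsin(√0.02) = 0.2897
- n = 2·[(1.960 + 0.842)/h]² = 187.02 per arm
- 187.02/0.95 = 196.9, so 197. Rounding up to 188 before allowing for loss gives 198.

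This figure does not depend on how item 3 is analysed.

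**Inputs for item 3.**

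- Evaluable patients per arm: 197 × 0.95 ≈ 187 (from 2.8).
- r, the within-arm correlation between the preoperative and the 24-hour value: **not in the document**. It is assumed over 0.2 to 0.7.

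**Formulas.** These assume a linear relation with the same slope and residual variance in both arms, on the log scale for iPTH.

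- Variance of the adjusted difference = (1 − r²) × variance of the unadjusted difference.
- Confidence interval width factor = √(1 − r²).
- Equivalent sample-size factor = 1/(1 − r²).
- Smallest difference detectable with 80% power, unadjusted = (1.960 + 0.842)·√(2/187) = 0.290 SD. Adjusted, it is 0.290·√(1 − r²).
- Adjusted power at 0.290 SD = Φ[2.802/√(1 − r²) − 1.960].

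| Assumed r | Variance removed (r²) | CI width factor | CI narrower by | Equivalent sample-size factor | Detectable difference (SD) | Power at 0.290 SD |
|---|---|---|---|---|---|---|
| 0 (unadjusted) | 0% | 1.000 | 0% | 1.00 | 0.290 | 80.0% |
| 0.2 | 4% | 0.980 | 2% | 1.04 | 0.284 | 81.6% |
| 0.3 | 9% | 0.954 | 5% | 1.10 | 0.276 | 83.6% |
| 0.5 | 25% | 0.866 | 13% | 1.33 | 0.251 | 89.9% |
| 0.7 | 49% | 0.714 | 29% | 1.96 | 0.207 | 97.5% |

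The gain is negligible at the bottom of the range and large at the top. The article does not show where in the range this trial lies.

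**The case against.** **The two-sample test is valid.** In a 1:1 randomized trial the starting level is balanced in expectation. It cancels from the between-arm difference, and chance imbalance is already reflected in the standard error. This stands. A reader might infer that the raw comparison confuses starting level with surgical loss, and so misstates the treatment effect. That would be a problem in judging an individual patient, but it does not bias the group contrast. Nor does the article define item 3 as a loss of function. It asks for a comparison of levels.

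**The article's silence on preoperative samples proves nothing.** This also stands. A reader might infer from the sampling times in 2.5 ("Intact parathyroid hormone (iPTH) levels will be measured at 24 hours postoperatively (i.e. the morning after surgery") that no preoperative iPTH or calcium is taken. But 2.5 covers postoperative care, 2.3 mentions a baseline assessment without listing it, and a condensed article commonly leaves laboratory lists to the full protocol. The opposite inference is not secure either. Exclusion criterion 2, "Associated hyperparathyroidism that requires associating a parathyroidectomy in the same surgical act", suggests some preoperative work-up, but the article does not say how the condition is established.

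**Covariates for a secondary outcome usually belong in an analysis plan, and r may be low because the operation comes between the two samples.** This stands in part. Section 2.8 states generic test families and does not rule out an adjusted analysis. It does, however, name a method that covers item 3, and that method has no covariate. Replacing a stated method with a more efficient one is different from asking for missing detail. A low r would make the gain small, as the table shows.

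**A rank test copes with values below a laboratory's detection limit, and ANCOVA on log iPTH does not do so by itself.** This is correct, and the fix has to provide for it.

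**Conclusion.** The point holds as one of efficiency. The stated analysis of secondary outcome 3 leaves out the patient's own preoperative value, and with it a means of absorbing part of the between-laboratory variation in iPTH. The loss is in precision only. Adjustment would narrow the 95% confidence interval by about 2%, 5%, 13% or 29% at an assumed r of 0.2, 0.3, 0.5 or 0.7.

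The size rests entirely on r, which the document does not give, and on the usual ANCOVA assumptions. The primary outcome and the 394 patients are unaffected. The documents do not support a conclusion that the comparison is biased, or that preoperative values are not collected.

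**What to change.** 1. Confirm that preoperative iPTH and corrected calcium are part of the baseline assessment (2.3) in both arms, measured in the same hospital laboratory as the 24-hour sample, and name them there.
2. In 2.8, make the main analysis of item 3 an ANCOVA of each 24-hour value on its own preoperative value, with iPTH on the log scale. State a rule for iPTH values below the detection limit, or use a rank-based ANCOVA.
3. Keep the t or Mann-Whitney comparison as a sensitivity analysis.
4. Fix this wording before the data are analysed, so that there is no later choice between raw and adjusted results.

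**Cost:** a change of analysis wording and, if the values are not already taken, at most one added item on the preoperative blood test. A few missing preoperative values will need a stated handling rule. The sample size and the primary analysis do not change.

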### Sample size and statistical analysis

2.8

In a previous single-center study, it was found that in a prospective cohort of patients in which ICG arteriography was performed before removal of the thyroid gland, the rate of permanent hypoparathyroidism was 0% as compared with 11.9% in a cohort of historical controls (14). Based on a more conservative approach, a rate of permanent hypoparathyroidism of 2% is estimated in the ICG angiography-guided thyroidectomy and 8% in the control group. Assuming 1:1 allocation, an alpha error of 5%, a statistical power of 80%, and a loss rate of approximately 5% in each group, 197 patients per arm will be needed. Therefore, a total of 394 patients will be recruited. It is estimated that these patients will be included in the study between January 2023 and December 2024.

Study variables will be collected by the researchers through clinical visits and results of laboratory analyses. Data will be stored in a codified electronic database specifically designed for the purpose of the study. Monitorization of study data will be performed by external personnel unaware of details of the study. To examine the benefits of identifying the vascular pattern of the parathyroid glands using an ICG angiography before thyroidectomy for preventing permanent hypoparathyroidism, a full analysis set will be performed, that is, all patients randomized who will be operated on, and followed postoperatively until permanent hypoparathyroidism will be resolved or for a maximum of 12 months after surgery. Categorical variables will be expressed as frequencies and percentages, and continuous variables as mean ± standard deviation or median and interquartile range (IQR) (25th-75th percentile). The Shapiro-Wilks test will be used to assess the normal distribution of data and the Levene’s test to assess homoscedasticity. Categorical variables will be analyzed with the chi-square test or the Fisher’s exact test, and quantitative variables with the Student’s *t* test or the Mann-Whitney *U* test according to conditions of application. The risk ratio (RR) and the 95% confidence interval (95%) will be calculated to assess the probability of permanent hypoparathyroidism. Univariate and multivariate logistic regression models adjusted by confounding variables will be performed to identify risk factors for permanent hypoparathyroidism. *P* < 0.05 is set as the significance level. The Statistical Package for the Social Sciences (SPSS) version 26 for Windows will be used for data analysis.

## Discussion

3

Permanent hypoparathyroidism, a feared complication of thyroidectomy, in particular after total thyroidectomy for cancer, leads to substantial morbidity making the patient dependent on replacement therapy for life (1). Therefore, the feasibility of a surgical innovation technique allowing to preserve “in situ” more well perfused parathyroid glands during thyroidectomy and, consequently, contributing to prevent postoperative hypoparathyroidism is a clinically relevant contribution. The use of an ICG angiography before removal of the thyroid gland for intraoperative identification of the vascular supply of the parathyroids involves a change in the way thyroidectomy is performed. Previous experience with the use of ICG angiography has been focused on assessing the degree of fluorescence based on a black and white scoring system as a reflection of the degree of vascularization of the glands. Angiography-guided thyroidectomy is a further step to identify the parathyroid glands by means of visualizing the feeding vasculature of each individual gland. Moreover, ICG angiography is an easy procedure that does not add much time to the operation or include complicated or difficult maneuvers given that preparation and injection of the fluorescent dye is very simple. The main expected results of this study are a lower rate of permanent hypoparathyroidism, and a higher number of well-vascularized parathyroid glands left *in situ* in the angiography-guided thyroidectomy as compared to conventional thyroidectomy, with statistically significant differences in the comparison of these variables between the study groups.

These results will provide robust evidence of the advantages of incorporating pre-thyroidectomy ICG angiographic detection of the vascular mapping of the parathyroid glands for preventing permanent hypoparathyroidism. Accordingly, angiography-guided thyroidectomy may be a recommended technical procedure for patients undergoing total thyroidectomy.

## Ethics statement

The study has been approved by the Clinical Research Ethics Committee of Hospital Universitari de Bellvitge (approval code PR0042/22). The patients/participants provided their written informed consent to participate in this study.
